# Evaluating an audit and feedback intervention for reducing antibiotic prescribing behaviour in general dental practice (the RAPiD trial): a partial factorial cluster randomised trial protocol

**DOI:** 10.1186/1748-5908-9-50

**Published:** 2014-04-24

**Keywords:** Prescribing, Antibiotics, Dental

## Abstract

**Background:**

Antibiotic prescribing in dentistry accounts for 9% of total antibiotic prescriptions in Scottish primary care. The Scottish Dental Clinical Effectiveness Programme (SDCEP) published guidance in April 2008 (2nd edition, August 2011) for Drug Prescribing in Dentistry, which aims to assist dentists to make evidence-based antibiotic prescribing decisions. However, wide variation in prescribing persists and the overall use of antibiotics is increasing.

**Methods:**

RAPiD is a 12-month partial factorial cluster randomised trial conducted in NHS General Dental Practices across Scotland. Its aim is to compare the effectiveness of individualised audit and feedback (A&F) strategies for the translation into practice of SDCEP recommendations on antibiotic prescribing. The trial uses routinely collected electronic healthcare data in five aspects of its design in order to: identify the study population; apply eligibility criteria; carry out stratified randomisation; generate the trial intervention; analyse trial outcomes.

Eligibility was determined on contract status and a minimum level of recent NHS treatment provision. All eligible dental practices in Scotland were simultaneously randomised at baseline either to current audit practice or to an intervention group. Randomisation was stratified by single-handed/multi-handed practices. General dental practitioners (GDPs) working at intervention practices will receive individualised graphical representations of their antibiotic prescribing rate from the previous 14 months at baseline and an update at six months. GDPs could not be blinded to their practice allocation. Intervention practices were further randomised using a factorial design to receive feedback with or without: a health board comparator; a supplementary text-based intervention; additional feedback at nine months. The primary outcome is the total antibiotic prescribing rate per 100 courses of treatment over the year following delivery of the baseline intervention.

A concurrent qualitative process evaluation will apply theory-based approaches using the Consolidated Framework for Implementation Research to explore the acceptability of the interventions and the Theoretical Domains Framework to identify barriers and enablers to evidence-based antibiotic prescribing behaviour by GDPs.

**Discussion:**

RAPiD will provide a robust evaluation of A&F in dentistry in Scotland. It also demonstrates that linked administrative datasets have the potential to be used efficiently and effectively across all stages of an randomised controlled trial.

**Trial registration:**

Current Controlled Trials ISRCTN49204710

## Background

The Scottish Dental Clinical Effectiveness Programme (SDCEP) was established in 2004 as a joint initiative of the National Dental Advisory Committee and NHS Education for Scotland (NES) with the aim of providing user-friendly evidence-based guidance in priority areas for dental healthcare in Scotland. The guidance it produces is designed to assist dental teams and to improve patient health by presenting advice and recommendations that are based on the best available information, thereby facilitating the translation of research evidence into practice and assisting in compliance to the ever changing regulatory framework of healthcare provision.

In April 2008, SDCEP published guidance for Drug Prescribing in Dentistry that is suitable for informing dental practitioners in the primary care sector, and applies to all patients who would be treated in the primary care sector in Scotland [1]. The guidance brought together advice and recommendations on dental prescribing from the British National Formulary (BNF) and the BNF for Children and from the National Institute for Health and Clinical Excellence and presented it in a readily accessible, problem orientated style. In August 2011, a second edition of Drug Prescribing for Dentistry was published by SDCEP. In addition, a ‘dental prescribing’ app for iPhone®, iPad®, and iPod touch® was launched in April 2012 [2].

Despite the introduction of the SDCEP guidance, there is wide variation in dental drug prescribing in Scotland. Antibiotic prescribing in dentistry accounts for 9% of total antibiotic prescribing in primary care in Scotland. In 2011, the overall use of antibiotics in dentistry was reported to be 7.6% higher than in 2010 [3]. General dental practitioners (GDPs) prescribe antibiotics regularly for the management of dental infections, but treatment is often guided by personal experience and knowledge [4,5], and in many cases antibiotics are prescribed inappropriately to patients with dental emergencies [6]. It is widely recognised that antimicrobial resistance is a major threat to public health and patient safety. Inappropriate antibiotic prescribing contributes to an increasing risk of antimicrobial resistance [3].

In dentistry, there is ample evidence that the implementation of guidance by dental professionals is variable and understanding how to change this is limited [7]. However, there is a lack of robust, generalisable evidence on how best to promote the translation of guidance into practice. This was highlighted in the Health Technology Assessment (HTA) systematic review of the effectiveness and efficiency of guideline dissemination and implementation strategies [8], which found evidence that although dissemination and implementation of guidance could lead to compliance with recommendations, the effect varied both within and across interventions.

Audit and Feedback (A&F) is defined as ‘any summary of clinical performance of healthcare over a specified period of time’ aimed at changing health professional behaviour [9]. A&F is a commonly used approach and has consistently demonstrated small to moderate sized effects, [9] though predicting the clinical circumstances where effects will be moderate and those where effects are small has been elusive [10].

In Scotland, routinely collected electronic healthcare data (*e.g.*, number of claims for treatment and number of prescription items dispensed) are available at the level of the individual GDP. One way in which current practice may be enhanced is by the provision of individualised feedback on antibiotic prescribing to GDPs. Another way is with the addition of behaviour change techniques (BCTs). A BCT is a ‘systematic procedure included as an active component of an intervention designed to change behaviour’ [11]. BCTs are the ‘active ingredients’ in an intervention (*i.e.*, they are the proposed mechanisms of change). Guidelines tend to be lengthy, and it is unknown whether providing clinicians with a distillation of the guidelines solely into the BCTs could be an advantageous way of enhancing implementation and changing behaviour.

The RAPiD (Reducing Antibiotic Prescribing in Dentistry) trial will compare the effectiveness of individualised A&F strategies for the translation into practice of SDCEP recommendations on antibiotic prescribing. The objectives of the trial relate to antibiotic prescribing behaviour at dental practice level. The research question being addressed is: In comparison to current practice, does the provision of individualised feedback on antibiotic prescribing at differing intervals (*i.e.*, 0 and 6 months ± 9 months), with or without a comparator, with or without a text-based intervention reiterating the ‘active ingredients’ within the SDCEP recommendations on antibiotic prescribing lead to a reduction in antibiotic prescribing in dental primary care in Scotland?

In addition, a process evaluation will explore the acceptability of the individualised A&F strategies and identify barriers and enablers to evidence-based antibiotic prescribing practice in dentistry. The RAPiD trial is being conducted as part of NES’s TRiaDS (Translation Research in a Dental Setting) programme [12]. At writing (December 2013), data collection and delivery of the individualised baseline and six months A&F interventions have taken place.

## Methods

### Trial Design

The RAPiD trial is a 12-month partial factorial cluster randomised controlled trial conducted in NHS General Dental Practices across Scotland. A cluster design was used to reduce contamination within dental practices. A factorial design was used to assess the effect of the three A&F strategies (*i.e.*, inclusion of a comparator, inclusion of a text-based intervention and the interval between receiving feedback). We will also explore the effects of the interventions combined. A control group was included to test the effectiveness of any form of A&F strategy (Figure 1).

**Figure 1 F1:**
[figure not shown]
Study design.

The trial uses routinely collected electronic healthcare data in five aspects of the trial design in order to: identify the study population; apply eligibility criteria; carry out stratified randomisation; generate individualised feedback for the trial intervention; and analyse trial outcomes.

Permission was granted by the NHS National Services Scotland (NSS) Privacy Advisory Committee (PAC Ref: 10/12) to link data from the Management and Dental Accounting System (MIDAS) database with the Prescribing Information System for Scotland (PRISMS) database.

### Initial data linkage and processing

Information Services Division (ISD) of NHS National Services Scotland (NSS) holds the MIDAS and PRISMS databases. The MIDAS database contains claims information relating to all courses of NHS dental treatment provided by GDPs in the General Dental Service since 1990. The PRISMS database contains information for all primary care prescriptions dispensed in community pharmacies (including dental prescriptions) since April 2004.

ISD supplied the TRiaDS Programme Office with the treatment data extracted from MIDAS and with monthly dental prescribing PRISMS data. The data from MIDAS and PRISMS were linked to a further extract from MIDAS containing contact information for GDPs and dental practices across Scotland. This extract was supplied by the Practitioner Services Division (PSD) of NHS NSS and listed all GDPs practising as at April 2013.

The GDP list number was used as the single common identifier. The list number is common to both MIDAS and PRISMS (in PRISMS the list number is used as the Prescriber ID) and is a unique number issued to GDPs by Health Boards in order for them to submit item-of-service and registration claims for payment. The linked dataset does not contain any patient identifiable information and was processed in accordance with the Data Protection Act 1998.

### Intervention development

#### Individualised audit and feedback interventions

Monthly prescribing volume was determined by the number of antibiotic items (BNF section 5.1) prescribed in the General Dental Service and subsequently dispensed each month. The monthly number of claims was determined as the number of ordinary list claims for treatment recorded in MIDAS each month (*i.e.*, claims made for NHS treatment carried out for patients registered under a dentist’s standard list number at a given location). Claims made on other lists, *e.g.*, emergency, trainer, and assistant were excluded. After the six-month intervention was delivered, the status of some ordinary lists in MIDAS was reclassified as public dental service and these will be included thereafter. For each individual GDP, the prescribing rate was calculated as the monthly number of items dispensed divided by the mean monthly number of claims (multiplied by 100). The initial feedback contained retrospective prescribing rates taken from the previous 14 months (November 2011 to December 2012). Monthly prescribing rates for health boards were similarly calculated based on total antibiotic items prescribed and total number of treatment claims within each health board.

### Development of the text based intervention

The sections on bacterial infections, in the published SDCEP clinical guidance on ‘Drug Prescribing for Dentistry’, were coded for the presence/absence of BCTs using the 2012 BCT taxonomy [13,14]. Two BCTs were identified: instruction on how to perform the behaviour; and provide information about health consequences of performing the behaviour. These BCTs were therefore selected for inclusion within a text-based intervention. The SDCEP guidance included behavioural instruction relating to pre-decision processes, *i.e.*, whether or not it is appropriate to prescribe antibiotics; and post-decision processes, *i.e.*, ways to optimise antibiotic prescribing once the decision to prescribe had been made. We chose to include only the BCTs that focussed on the pre-decision processes. Where possible, the exact wording from the SDCEP guidance document was used. A number of potential BCTs coded in the guidance had to be excluded from the final text-based intervention due to insufficient specification of behaviour. For example, the behaviour ‘take care’ within ‘take care when prescribing these antibiotics to vulnerable groups’ was not explicit enough to be included as ‘instruction on how to perform the behaviour’. The wording of text-based intervention used in the trial is:

‘Prescribing courses of antibiotic treatment can encourage the development of antimicrobial resistance and therefore must be kept to a minimum’.

‘As a first step in the treatment of bacterial infections, use local measures. For example, drain pus if present in dental abscesses by extraction of the tooth or through root canals, and attempt to drain any soft-tissue pus by incision’.

‘This should be the first step even if patients request antibiotics and even when time is short’.

‘Antibiotics are appropriate for oral infections where there is evidence of spreading infection, systemic involvement or persistent swelling despite local treatment’.

‘Use antibiotics in conjunction with, and not as an alternative to, local measures’.

The development of the text-based intervention is reported in more detail in Additional file 1.

### Study population and eligibility

Practice addresses and the names of all GDPs working in NHS General Dental Practices across the 14 Scottish Health Boards were identified from the April 2013 PSD GDP list.

### Dental practice inclusion criterion

NHS General Dental Practices across the 14 Health Boards in Scotland.

### Dental practice exclusion criteria

Practices in mainland Health Boards in which any GDPs were salaried (Salaried GDPs are used as a proxy to identify community and emergency dental services). Predominantly due to geography, the majority of dental services in the Island Health Boards are provided by the NHS salaried service. For this reason, practices with salaried GDPs in the Island Boards are not excluded).

General Dental Practices where no ordinary list claims were made in more than 6 months out of the most recently available 12 months of MIDAS data at the time of the baseline intervention (January to December 2012).

### GDPs inclusion criteria

For the baseline intervention, GDPs listed by PSD as currently practicing in April 2013.

For the six-month intervention, GDPs listed by PSD as currently practicing in October 2013.

For the nine-month intervention, GDPs listed by PSD as currently practicing in January 2014.

### GDPs exclusion criterion

GDPs with no name recorded in the PSD list.

### Randomisation and allocation

All eligible practices (n = 795) were simultaneously randomised by AE at the beginning of the trial before any baseline feedback data were issued. The allocation schedule for random assignment was computer generated. Practices were ordered randomly, with the first 632 practices being allocated to an A&F intervention and the remaining practices being allocated to the control group. Each of the 632 intervention practices was allocated to one of the eight subgroups (see Figure 1) with an even allocation so that 79 practices were randomised to each subgroup. Randomisation was also be stratified by single-handed/multi-handed practices.

### Initial and follow-up procedures

All GDPs working in the 632 practices allocated to an intervention group received feedback (*i.e.*, feedback on antibiotic prescribing ± a comparator, ± a text based intervention) at baseline (May 2013) and updated feedback at six months (Nov 2013) (Figure 1). At nine months (February 2014), a further round of feedback will be delivered to GDPs in 50% of practices allocated to an intervention group (Figure 1). All intervention documents will be in paper form and delivered by post (Figure 2). These will be accompanied by a personalised cover letter providing information about the study and contact details for the TRiaDS Programme Office in the event of questions or requests for further information (Additional file 2).

**Figure 2 F2:**
[figure not shown]
Example feedback intervention document (anonymised with pseudonym).

The feedback at six months is in the same format as the baseline feedback but contains a further six months of prescribing rate data in addition to the 14 months of data fed back at baseline. The nine-month feedback will again be of a similar format. Additional PRISMS and MIDAS data were obtained from ISD to include data up to June 2013 for the six-month feedback and will be obtained to September 2013 for the nine-month feedback. The linked data relating to the 795 included practices from these updated datasets will also be linked to the list of eligible GDPs published by PSD (in October 2013 for the six-month update, in January 2014 for the nine-month update). Updated feedback sheets will be sent to GDPs at practices randomised to the intervention group. It is recognised that some GDPs and practices may be lost to follow-up (*e.g.*, if a practice closes or a GDP stops practising in Scotland).

### Outcomes

All outcomes pertain to cluster level (*i.e.*, dental practices).

The primary outcome is the total number of antibiotic items (from Section 5.1 of the British National Formulary [15]) dispensed per 100 claims over the 12 months from May 2013 to April 2014.

The secondary outcomes are:

1. Total number of Amoxicillin 3 g items dispensed per 100 claims over the 12 months from May 2013 to April 2014 [16].

2. Total number of ‘second-line’ antibiotic items (Clindamycin, Co-amoxiclav, Clarithromycin) [1] dispensed per 100 claims over the 12 months from May 2013 to April 2014.

3. Total defined daily doses of antibiotics [17] (from Section 5.1 of the British National Formulary [15]) dispensed per 100 claims over the 12 months from May 2013 to April 2014.

4. Total defined daily doses of Amoxicillin 3 g dispensed per 100 claims over the 12 months from May 2013 to April 2014.

5. Total defined daily doses of ‘second-line’ antibiotics (Clindamycin, Co-amoxiclav, Clarithromycin) [1] dispensed per 100 claims over the 12 months from May 2013 to April 2014.

### Data collection and processing

#### Schedule of data collection

MIDAS and PRISMS data are updated routinely by ISD on a monthly basis with a time lag of between two and three months. Updates of data will be received by the TRiaDS Office every month throughout the duration of the trial. Data covering the period up to 31 December 2012 was received in March 2013 and used for the intervention at baseline. Data up to 30 June 2013 was received in September 2013 and used for the six-month intervention (feedback was disseminated on 1 November 2013). Similarly, data up to 30 September 2013 will be used for the nine-month intervention (feedback will be disseminated on 1 February 2014).

### Analysis plans

#### Statistical analysis

Outcomes will be aggregated and analysed at the practice level. The analysis will estimate the effect of each intervention compared with current practice and will also estimate the differential effect between interventions (*i.e.*, inclusion of a text-based intervention, frequency of feedback and inclusion of a comparator). We will perform main effects analyses of covariance on the 12-month prescribing rate, adjusting for the pre-intervention yearly prescribing rate, practice size (single-handed/multi-handed), and the annual number of treatment claims submitted by the practice. The model fitting strategy will test the practice size variable (design), then the pre-intervention prescribing rate (covariate), and lastly a categorical variable (intervention) will be included to correspond with the main effects of the different interventions. The same approach will be used for all prescribing behaviours under investigation.

We will investigate whether larger effects of the interventions are observed for practices reporting higher pre-intervention levels of prescribing (defined as upper quartile practices). Additionally, to test for a reduction in the spread of prescribing levels, we will apply Levene’s test for equality of variances between the pre-intervention and intervention phases.

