### Sample size

The sample size calculation is based on aggregated practice level antibiotic prescribing. There will be 795 practices participating in the trial, of which 632 practices will be randomised to the intervention group. Each of the eight sub-level experimental units in the intervention group will have 79 practices. This is the required sample size to achieve 80% power (with two-sided alpha of 2.5% allowing for multiple comparisons) to detect a 10% difference in overall antibiotic prescribing between intervention groups. This applies to the comparison between A&F only (n = 316) and A&F with a text-based intervention (n = 316), the comparison between feedback at zero, six, and nine months versus zero and six months only and the comparison between those with and without a Health Board comparator. The sample size has been reduced using the correction described by Borm *et al*. for trials with correlated data [18]. The comparison between the control group (n = 163) and the intervention group (n = 632) will have 80% power to detect a 12% decrease in overall antibiotic prescribing.

The sample size calculation is based on prescribing activity recorded in PRISMS for the 1,799 dentist lists in Scotland known to be prescribing throughout the year ending June 2010. The mean number of antibiotic items prescribed per list was 141.1 with an SD of 140.9. The correlation with the year ending June 2009 is 0.91.

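### The 632 v 163 comparison with control rests on an equal-variance ANCOVA although the plan asks whether spread narrows; if residual spread falls under feedback, its confidence interval is somewhat too narrow

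*Protocol article*

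**What the plan says.** The relevant statements are all in the protocol article.

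- **Model (Statistical analysis).** "We will perform main effects analyses of covariance on the 12-month prescribing rate", adjusted for the pre-intervention rate, single- or multi-handed status and annual claims. The same approach serves every outcome. The rate is analysed untransformed, and no variance structure or standard-error estimator is named.
- **Spread (Statistical analysis).** Levene's test is planned "to test for a reduction in the spread of prescribing levels". It compares the pre-intervention phase with the intervention phase. The section also asks whether effects are larger in upper-quartile practices.
- **Allocation (Randomisation and allocation).** Practices were put in random order, "with the first 632 practices being allocated to an A&F intervention and the remaining practices being allocated to the control group". That gives 632 v 163, a ratio of 3.88 to 1.
- **Power (Sample size).** The control comparison "will have 80% power to detect a 12% decrease in overall antibiotic prescribing". The factor comparisons, 316 v 316, are sized with "two-sided alpha of 2.5% allowing for multiple comparisons" and are meant "to detect a 10% difference in overall antibiotic prescribing between intervention groups".

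**The concern.** ANCOVA in its ordinary form estimates one residual variance and applies it to both arms. When the arms are the same size, this does little harm even if the variances differ. When one arm is almost four times the other, it matters which arm is more variable. If the larger arm is the less variable one, the pooled variance is too low for the small arm, and the small arm supplies most of the uncertainty.

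The protocol raises that possibility itself by asking whether feedback narrows the spread of prescribing. A percentage reduction that acts proportionally on an untransformed rate would also shrink the intervention arm's residual SD by the same percentage, without any separate effect on spread.

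At stake is the interval for any feedback v current practice, which is the reason the control group was included. It would claim more precision than the data hold. The planned Levene's test would not reveal this, because it compares phases rather than arms, and marginal spread rather than ANCOVA residuals.

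**Working it through.** **Inputs from the Sample size section.** 632 and 163 practices; a 12% decrease; "The mean number of antibiotic items prescribed per list was 141.1 with an SD of 140.9"; correlation between years 0.91. These are list-level figures, the only ones given. The standard-error ratios below do not depend on the absolute SD.

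**Assumed input.** k = residual SD under feedback divided by residual SD under control. The protocol gives no value, so a range is shown.

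**1. The plan's own power figure.**
- Residual SD = 140.9 × √(1 − 0.91²) = 58.42.
- Equal-variance SE = 58.42 × √(1/632 + 1/163) = 5.13.
- Effect = 0.12 × 141.1 = 16.93.
- Power is 85.5% at two-sided 2.5% and 91.0% at two-sided 5%. The stated 80% is therefore not reproduced exactly, but it is conservative at 2.5%.
- The 316 v 316 comparison for a 10% difference gives 78.7% at two-sided 2.5%, close to the stated 80%.

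**2. Standard error for 632 v 163.** In units of the control residual variance:
- true variance = 1/163 + k²/632
- pooled variance = [(163 + 632k²)/795] × (1/163 + 1/632)

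At k = 0.90 the true variance is 0.007417 and the pooled variance 0.84896 × 0.007717 = 0.006552. The SE ratio is √(0.006552/0.007417) = 0.940, that is 4.73 against 5.03 items. Controls supply 0.006135/0.007417 = 83% of the true variance, while 632/795 = 79% of the practices behind the pooled estimate are intervention practices.

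| k | Model SE / true SE | Coverage of nominal 95% interval |
|---|---|---|
| 1.00 | 1.00 | 95.0% |
| 0.95 | 0.97 | 94.3% |
| 0.90 | 0.94 | 93.5% |
| 0.88 | 0.93 | 93.1% |
| 0.80 | 0.88 | 91.5% |

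**3. Simulation of a 12% proportional effect.** 632 v 163, correlation 0.91, lognormal or gamma rates with an assumed between-practice coefficient of variation of 0.5 to 1.0. The model-based SE is up to 9% too small. Coverage is 92.8% to 93.2% with the model SE and 94.8% to 95.4% with HC3.

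**4. Where the error is small or absent.**
- *Only the baseline slope flattens.* With 10% or 20% flattening and residual SD unchanged, the marginal SD falls by about 8% or 16%: √(0.819² + 0.1719) = 0.918 and √(0.728² + 0.1719) = 0.838. The simulated SE ratio stays at about 0.96 to 1.00.
- *No effect on mean or spread.* k = 1, and the ordinary test and the HC3 test both hold their level.
- *Smaller intervention groups v control,* using the same pooled variance at k = 0.90. For 316 v 163 the SE is 4.7% too small (coverage 93.8%). For 79 v 163 it is 1.3% too small (coverage 94.7%).
- *316 v 316.* The comparison is balanced and almost unaffected.

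**5. Test level.** If the residual spread shrank 10% with no change in mean, a nominal 2.5% test would reject 3.5% of the time by formula and 3.6% to 4.2% in simulation (2.3% to 3.1% with HC3).

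**The case against.** The strongest reply has four parts.

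- **The variance estimator is not stated.** Equal variance is what ANCOVA implies when nothing more is said; the article does not write it down. A statistical analysis plan that is not shown may specify robust errors. This stands as a limit. The point is therefore about the assumption carried by the named model in this design, and not about a missing detail.
- **The plan does not predict narrowing.** A reader might infer that the trial expects a narrower spread, and that the standard error is therefore too small. The article supports neither step. It sets a test for a reduction in spread and gives no size, and the 12% is a detectable difference whose form, proportional or otherwise, is not specified.
- **The spread under test is a different quantity.** Levene's test concerns marginal spread between phases. The ANCOVA standard error depends on residual spread between arms given baseline. With a correlation of 0.91 the first can fall while the second hardly moves, and flattening of the slope is the mechanism most naturally suggested by the upper-quartile question. This stands, and it is why the conclusion is conditional.
- **Type I error is hardly at risk.** If feedback does nothing, the level is correct. Inflation needs the spread to shrink with the mean unchanged, so that rises among low prescribers offset falls among high ones. Nothing in the article suggests that. The harm is chiefly to interval coverage.

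What the reply does not remove is the combination of a 3.88 to 1 allocation, an untransformed rate, an effect expressed as a percentage, and a model that is anticonservative if the larger arm becomes less variable.

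**Conclusion.** The point holds in conditional form. If feedback lowers the residual SD by 10% to 12%, the model-based standard error for any feedback v control is about 6% to 9% too small, and a nominal 95% interval covers about 93%. This rests on an assumed residual SD ratio, on a correlation of 0.91 carrying over from lists to practices and, for the simulated figures, on the assumed distributions.

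A reader might go further and infer that the control comparison is invalid or that its false-positive rate is generally inflated. The documents do not support that: the size is modest, the level is intact when feedback changes neither mean nor spread, and the three factor comparisons are essentially untouched. This is a cheap improvement to an otherwise sound model.

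**What to change.** Keep the ANCOVA, its covariates and the untransformed rate. Add one sentence: for all outcomes, tests and confidence intervals for comparisons with control use heteroskedasticity-consistent (HC3) standard errors, or a model with separate residual variances for control and intervention practices. HC3 leaves the point estimate unchanged and holds its level when the variances are equal. If the analysis plan already specifies this, no change is needed.

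The cost is a slightly wider interval and roughly 1 to 3 points of power when the variances do differ. By formula at k = 0.88 and two-sided 2.5%, 16.93/5.012 = 3.378. The equal-variance test then has apparent power Φ(3.378 − 2.241 × 0.928) = 90.3%, and a test with the correct standard error has Φ(3.378 − 2.241) = 87.2%. In one simulated case the fall is from 0.908 to 0.894. Both remain above the stated 80%.
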